3. Subgroup analyses	The percentage of women within each of the normal, overweight, and obese BMI categories will be similar with respect to being with the IOM target GWG for each category	Proportion of women in each BMI category who reach appropriate GWG according to the IOM guideline for GWGs	Regression analysis including the interaction term of BMI group X Intervention group
4. Sensitivity analyses	Combined Nutrition + Exercise Intervention leads to a greater percentage of women who achieve GWG within current recommendations when compared to standard care	Primary outcome only	***•*** Generalized estimating equations ***•*** Random-effects model

IMPORTANT REMARKS:

In all analyses, results will be expressed as difference or OR (95% CI) and associated *p* values, as appropriate

Bonferroni method will be used to adjust the overall level of significance for multiple secondary outcomes

We will examine residuals to assess model assumptions

The GEE [76] is a technique that allows to specify the correlation structure between patients within a site and this approach produces unbiased estimates under the assumption that missing observations will be missing at random. An amended approach of weighted GEE will be employed if missingness is found not to be at random [77]

*Infant growth outcomes at 6 months will be adjusted for feeding type (duration of breast feeding from birth to 6 months)

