### Statistical methods

The analysis and reporting of the results will follow the SPIRIT statement for reporting RCTs [53]. The process of patient selection and flow throughout the study will be summarized using a flow-diagram (Fig. 2).

The results of patient baseline characteristics and outcome variables (both primary and secondary) will be summarized using descriptive summary measures: expressed as mean (standard deviation) or median (range) for continuous variables and n (%) for categorical variables. All statistical tests will be performed using two-sided tests at the 0.05 level of significance. Binary outcomes will be analyzed using logistic regression and continuous outcomes will be analyzed using linear regression. All analyses will account for stratification by including study site and participants’ BMI category in the models. For all models, the results will be expressed as estimate of the difference for continuous outcomes (odds ratio [OR] or relative risk [RR] for binary outcomes), corresponding two-sided 95% confidence intervals (CI) and associated *p* values. *P* values will be reported to three decimal places with values < 0.001 reported as < 0.001. The Hosmer–Lemshow will be used to assess goodness-of-fit for logistic regression and explore the residuals to assess goodness-of-fit and model assumptions for linear regression.

An intention-to-treat principle will be adopted to analyze all outcomes. Multiple-imputation will also be used to handle missing data during data collection. Sensitivity analyses will be performed using some of the commonly used RCT patient-level methods (e.g. generalized estimating equations, the random-effect model which account for the potential correlation within sites, etc.) to assess the robustness of the results [54]. All the analyses will be done using SAS 9.2 (Cary, NC, USA) or SPSS 13 (Chicago, IL, USA). Table 2 provides a summary of the planned methods of analyses for each outcome and subgroup.

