### Power calculation

The sample size calculation for the core study is based on the test of the null hypothesis that the percentages of women with GWG within IOM guidelines in the two populations (intervention and control) are equal. To account for the uncertainty in these prior estimates, we calculated the sample size for different values of the percentage of women with weight within IOM guidelines in the control group in the range of 50–65%, with a risk difference of 15%, 20%, 25%, and 30%. While initially we targeted a total sample size of 350, the constraints of our funding timelines (which include a one-year CHIR grant extension) and a recruitment rate that was less than projected despite our best efforts, we revised our desired sample size to 242. Based on our a priori calculation, a sample size 111 per group corresponds to an absolute difference of 30% with our Nutrition + Exercise intervention, resulting in 30% of women in the treatment group having a GWG exceeding the IOM recommendations compared to 65% in the control group. With the revised sample size (i.e. assuming a 1:1 allocation ratio), the study will have power of 80% to yield a statistically significant result assuming a binomial distribution (using an intention-to-treat principle for the analysis) of the difference between percentages of women with GWG within IOM guidelines at alpha = 0.05. We hope to increase the sample size to 242 total participants in order to allow us to account for the two stratification variables – site (2 degrees of freedom) and baseline BMI strata (3 degrees of freedom).

The calculated sample size for the secondary outcome of maternal bone biomarker status is a total of 177 participants (allocation 1:1, α = 0.05, β = 20 for two-group t-test), based on literature with similar outcomes [55, 56]. A sample size was also calculated for the secondary outcome of infant whole body minus the head BMD. The total is 240 participants (allocation 1:1, α = 0.05, β = 20 for two-group t-test) based on the literature with similar primary outcomes in infant populations [57, 58]. For both sample sizes, a 15% attrition rate was calculated as a precaution in this type of clinical trial with follow-up.

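### The secondary sample sizes assume a 0.05 test level, but Table 2 applies Bonferroni to an unfixed list of outcomes, so the planned 80% power does not hold; the infant calculation also uses BMD where the listed outcome is BMC

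*Protocol article*

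**What the plan says.** The Power calculation section gives two secondary sample sizes. For the mothers, "The calculated sample size for the secondary outcome of maternal bone biomarker status is a total of 177 participants", with the specification "allocation 1:1, α = 0.05, β = 20 for two-group t-test), based on literature with similar outcomes". For the infants, "A sample size was also calculated for the secondary outcome of infant whole body minus the head BMD", and "The total is 240 participants (allocation 1:1, α = 0.05, β = 20 for two-group t-test". Both totals include a 15% attrition allowance. Neither calculation mentions multiplicity, and neither gives an effect size or standard deviation.

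The remarks under Table 2 add that "Bonferroni method will be used to adjust the overall level of significance for multiple secondary outcomes". The number of tests is not given. The Statistical methods section states the general level: "All statistical tests will be performed using two-sided tests at the 0.05 level of significance".

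The Outcome measurements section describes the secondary outcomes twice. The bulleted list has five bone markers in maternal and cord blood, three maternal DXA measures and one infant DXA measure. It puts fat mass, metabolic status, blood pressure, pregnancy outcomes and infant birth outcomes under other outcomes. Table 2 puts those same measures in its secondary row. In both places the infant bone outcome is whole body minus the head BMC.

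**The concern.** A sample size that gives 80% power at 0.05 gives less at 0.05/m. The plan adopts a Bonferroni rule and then quotes sample sizes that ignore it. Because the list and Table 2 disagree on which outcomes are secondary, the divisor is open as well, and could be settled after results are known.

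Bone health is the stated secondary objective, is part of the over-arching hypothesis, and is the reason for the six-month extension. A non-significant bone result could be read as coming from a test with 80% power when the plan's own rule gives it clearly less. A significant one could be disputed over which threshold applied. The infant calculation adds a separate mismatch: the variable that was sized is not the variable that is listed.

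**Working it through.** **Inputs from the protocol article.** Totals 177 and 240, 1:1 allocation, alpha 0.05, beta 20 (read as 20%) and 15% attrition, all from Power calculation; two-sided testing, from Statistical methods; planned total 242, from Power calculation; 87% retention to 36–38 weeks, from the Discussion.

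**Reproducing the plan's figures.** The totals cannot be rebuilt from first principles without an effect size. The attrition step does reproduce: 150/0.85 = 176.5, rounded up to 177, and 204/0.85 = 240. The evaluable numbers are therefore 75 and 102 per arm.

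**Counting the family.**
- Outcome list: 5 maternal markers + 5 cord markers + 3 maternal DXA + 1 infant DXA = 14. Counting each marker once across maternal and cord blood gives 5 + 3 + 1 = 9.
- Table 2, secondary row: those 14 + fat mass 1 + glucose, lipid profile, leptin and adiponectin 4 + blood pressure 2 + gestational diabetes and pre-eclampsia 2 + infant birth weight z-score and fat mass 2 = 25. The lipid profile is counted once; counting repeated maternal sampling times separately would raise the total.

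**Power at the stated sizes.** No effect size is needed. If a design has 80% power at two-sided 0.05, its standardised signal is 1.960 + 0.842 = 2.802 (normal approximation). Power at level 0.05/m is then Φ(2.802 − z), where z is the two-sided critical value at 0.05/m. The result is the same for both outcomes.

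| m | 0.05/m | z | Power |
|---|---|---|---|
| 1 | 0.05 | 1.960 | 80% |
| 5 | 0.01 | 2.576 | 58.9% |
| 9 | 0.0056 | 2.773 | 51.1% |
| 14 | 0.0036 | 2.914 | 45.5% |
| 25 | 0.002 | 3.090 | 38.6% |

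The noncentral t gives nearly the same: about 45% for m = 14 and 38% for m = 25.

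**Power at the planned 242.** With 15% loss there are 242 × 0.85 / 2 = 102.85 per arm; with 13% loss, 242 × 0.87 / 2 = 105.27. The signal scales with the square root of n.
- Maternal markers: 2.802 × √(102.85/75) = 3.281 and 2.802 × √(105.27/75) = 3.319.
- Infant bone: 2.802 × √(102.85/102) = 2.813 and 2.802 × √(105.27/102) = 2.846.

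| m | Maternal markers (15% to 13% loss) | Infant bone (15% to 13% loss) |
|---|---|---|
| 1 | 90.7–91.3% | 80.3–81.2% |
| 9 | 69.4–70.8% | 51.6–52.9% |
| 14 | 64.3–65.7% | 46.0–47.3% |
| 25 | 57.6–59.1% | 39.1–40.4% |

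**Size needed for 80% after Bonferroni.** The implied standardised differences are d = 2.802 × √(2/75) = 0.457 and 2.802 × √(2/102) = 0.392. With n per arm = 2(z + 0.842)²/d², rounded up:
- Maternal markers: 135 (m = 14) to 148 (m = 25) per arm, so 270 to 296 evaluable, or 318 to 349 recruited after dividing by 0.85.
- Infant bone: 184 to 201 per arm, so 368 to 402 evaluable, or 433 to 473 recruited.

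**Variable.** Power calculation sizes BMD; the outcome list and Table 2 name BMC. Without the effect size or SD for either, power for BMC cannot be derived from the article.

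**The case against.** The strongest objection is that the figures at 177 and 240 do not describe this trial. It plans 242, and at that size maternal markers have about 58–66% power after adjustment for 25 to 14 tests, and about 91% without adjustment. This stands. A reader might infer that both bone outcomes have even odds or worse; that holds for infant bone at m = 14 or 25, but not for maternal markers.

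The values of m are counts made from the text. The composition of the family may be fixed in an analysis plan that is not shown, and a smaller family gives higher power. This also stands, but even five tests give only 59% at the stated sizes. The disagreement between the list and Table 2 is in the printed article, not a detail left for later.

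The blanket 0.05 level need not contradict Table 2: it can be read as a general level that the Bonferroni remark modifies. That reading is fair, so only a clarification is needed there.

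A reader might also infer that attrition already undermines the infant calculation. The documented figures do not show this: 242 × 0.87 = 210, against 204 needed. Retention at 36–38 weeks does not cover later loss or unusable scans, but the article gives no figure for either.

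The BMD mismatch is softened because the data collection section says that infant results are expressed as both BMC and BMD. BMD is therefore measured, but it is still not the listed secondary outcome.

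Finally, the primary analysis is untouched, and stricter testing does not inflate false positives. Both are true; the problem lies in the power claimed for the secondary outcomes.

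**Conclusion.** The point holds. The secondary sample sizes and the multiplicity rule do not match, so 80% power is not what the plan delivers for either outcome at the stated sizes. Power per outcome there is about 51%, 45% or 39% for 9, 14 or 25 tests. At 242 recruited with 13–15% loss, and 14 to 25 tests, it is about 39–47% for infant bone and 58–66% for maternal markers.

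These figures assume that beta 20 means 20%, that the literature effects behind 177 and 240 are correct, and that Bonferroni divides 0.05 equally. For the infants they also assume that loss to the six-month scan stays within 13–15%. They describe each outcome separately, not the chance of finding any bone effect, so they should not be read as the power of the bone objective as a whole. For infant bone they describe the BMD calculation; the article establishes no power for BMC.

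**What to change.** 1. Use one list of secondary outcomes in both the outcome section and Table 2, and state the number of tests m, including how maternal and cord markers and repeated samples are counted.
2. Restate the power of the sized secondary outcomes at 0.05/m for the planned 242 after attrition, giving the effect size and SD used.
3. Redo the infant calculation for whole body minus the head BMC, or align the listed outcome with the variable that was sized.
4. Add to Statistical methods that the 0.05 level is subject to the Bonferroni adjustment for secondary outcomes.

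These are changes of text and recalculation, with no new participants or procedures. The cost is that the stated secondary power becomes less favourable. Naming a single key secondary outcome, tested only if the primary is significant, is an option but is not required. It could not rest on the existing infant figure, which is for BMD.

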## Outcome measurements

Primary and secondary outcomes are summarized in Table 2 and described below.Primary outcome○ GWGSecondary outcomes○ Maternal and cord blood circulating bone markers: PINP, CTX-I, IGF-1, 25(OH)D, 1,25dihydroxyvitamin D○ Maternal bone status at six months postpartum: whole-body bone mineral content (BMC), whole body BMD, lumbar spine BMD○ Infant bone status at six months of age: whole body minus the head BMCOther outcomes○ Maternal body weight and fat mass○ Maternal metabolic status (including fasting glucose and lipid profiles, leptin and adiponectin)○ Maternal blood pressure○ Maternal pregnancy outcomes such as gestational diabetes and pre-eclampsia○ Infant birth outcomes such as birth weight and body fat mass at six months○ Safety outcomes○ Quality of life using the EQ-5D questionnaire○ Healthcare costs○ Maternal and cord blood gene variant profiles

**Table 2 Tab2:** Analysis plan: objectives, outcomes, hypotheses, and methods of analysis

Objective	Hypothesis	Outcome measure (type of outcome: B = binary or C = continuous)	Methods of analysis
1. Primary	An experimental combined Nutrition + Exercise intervention will increase the percentage of pregnant women who achieve GWG within current recommendations when compared with standard care provided in the primary care community setting	Proportion of women who are within the BMI appropriate GWG according to the IOM guideline for GWGs (B)	Logistic regression
2. Secondary	An experimental combined Nutrition + Exercise intervention will lead to better maternal and child bone health outcomes when compared to standard care	*• Maternal and cord blood circulating bone markers (C)* ○ Bone biomarkers: PINP, CTX-I, IGF-1, 25(OH)D, 1,25(OH)_2_D *• Maternal bone status at 6 months postpartum (C)* ○ Whole body bone mineral content, whole body BMD, lumbar spine bone mineral density by DXA scan *• Maternal fat mass (C)* *• Maternal blood glucose, lipid profile, leptin, and adiponectin* *• Maternal blood pressure (C)* ○ Diastolic BP ○ Systolic BP *• Maternal pregnancy outcomes (B)* ○ Gestational diabetes ○ Pre-eclampsia *• Infant bone status at 6 months of age (C)* ○ Whole body minus the head bone mineral content by DXA scan *• Infant outcomes* ○ Birth weight z-score(C) ○ Body fat mass (B)	Regression analysis *We will use logistic regression for binary outcomes and linear regression for continuous outcomes

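### Holm's step-down procedure could replace single-step Bonferroni for the secondary outcomes: same familywise error, never fewer rejections, usually a small gain

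*Protocol article*

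**What the plan says.** The multiplicity rule stands in the remarks under Table 2 (Outcome measurements): "Bonferroni method will be used to adjust the overall level of significance for multiple secondary outcomes". No step-down or other sequential variant is named, so the natural reading is the single-step rule, which compares every secondary p value with 0.05/m, where m is the number of secondary tests. Statistical methods sets the level and sidedness: "All statistical tests will be performed using two-sided tests at the 0.05 level of significance".

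The article does not state m. The outcome list puts only bone outcomes under the secondary heading, beginning with "Maternal and cord blood circulating bone markers: PINP, CTX-I, IGF-1, 25(OH)D, 1,25dihydroxyvitamin D", followed by three maternal DXA measures and one infant DXA measure. The secondary row of Table 2 is wider; it also holds maternal fat mass, "Maternal blood glucose, lipid profile, leptin, and adiponectin", blood pressure, two pregnancy outcomes and two infant outcomes.

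On intervals, the Table 2 remarks begin: "In all analyses, results will be expressed as difference or OR (95% CI", and Statistical methods repeats two-sided 95% intervals for all models. Neither place mentions intervals adjusted for multiplicity.

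**The concern.** Single-step Bonferroni holds every p value to the strictest threshold, even after other hypotheses in the family have been rejected. Holm applies that threshold only to the smallest p value and relaxes it step by step. It needs no extra assumption and controls the same error. When a plan commits itself to Bonferroni without using the one thing Bonferroni offers over Holm (simple matching simultaneous intervals), it accepts a loss of power that it could avoid.

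At stake are the bone conclusions. The stated hypothesis is that one intervention improves maternal and infant bone outcomes across the set. If it does, several null hypotheses are false together, and a step-down method gains most in that setting. The point concerns only the choice of procedure, not the secondary sample sizes.

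**Working it through.** **No planned figure to reproduce.** Nothing stated in the article depends on Bonferroni versus Holm. The secondary sample sizes under Power calculation ("The calculated sample size for the secondary outcome of maternal bone biomarker status is a total of 177 participants" and, for infant bone, "The total is 240 participants") come without a difference or a standard deviation, so they supply no effect sizes for this check.

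**Inputs**
- Familywise level 0.05, two-sided (Statistical methods).
- m, counted from the article because it is not stated. From the outcome list: 5 markers + 3 maternal DXA + 1 infant DXA = 9. If the markers are tested in maternal and in cord blood: 10 + 3 + 1 = 14. From Table 2: 14 + fat mass 1 + glucose, lipids, leptin and adiponectin 4 + blood pressure 2 + pregnancy outcomes 2 + infant outcomes 2 = 25. The last count takes the lipid profile as one test and each outcome at one time point.
- Assumption: each true effect has 80% power at two-sided 0.05, a standardised effect of 1.96 + 0.84 = 2.80.
- Assumption: correlation between test statistics of 0 or 0.3.

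**Rules.** Order the p values p(1) ≤ … ≤ p(m). Bonferroni rejects every hypothesis with p ≤ 0.05/m. Holm compares p(1) with 0.05/m, p(2) with 0.05/(m−1), and so on, and stops at the first failure. Every Holm threshold is at least 0.05/m, so Holm rejects whatever Bonferroni rejects. The first threshold is the same, so the chance of at least one rejection is the same.

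**Bonferroni by formula.** Power per true effect is P(Z > c − 2.80), where c is the two-sided critical value at 0.05/m; the opposite tail is negligible. With no true effects and independent tests, familywise error is 1 − (1 − 0.05/m)^m.

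| m | 0.05/m | c | Power per true effect | Familywise error |
|---|---|---|---|---|
| 9 | 0.0056 | 2.773 | 51% | 0.0489 |
| 14 | 0.0036 | 2.914 | 46% | 0.0489 |
| 25 | 0.0020 | 3.090 | 39% | 0.0488 |

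**Holm by simulation** (100,000 replicates per setting, two-sided z tests; ranges cover correlations 0 and 0.3)

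| m | True effects | Bonferroni | Holm |
|---|---|---|---|
| 9 | 3 | 51% | 53% |
| 9 | 5 | 51% | 55% |
| 9 | 9 | 51% | 62–63% |
| 14 | 4 | 46% | 47% |
| 14 | 7 | 46% | 49% |
| 14 | 10 | 46% | 51% |
| 14 | 14 | 46% | 55–56% |
| 25 | 7 | 39% | 40% |
| 25 | 14 | 39% | 41–42% |
| 25 | 25 | 39% | 46–48% |

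With a single true effect the two methods are practically equal (m = 14: 45.6% for both). No replicate had a Bonferroni rejection that Holm missed. Familywise error stayed below 5% for both methods, reaching about 4.9% when no effect was real and the tests were independent. Seen per trial, with m = 14 Holm declares at least one outcome that Bonferroni misses in about 19% of trials with 7 real effects, 38% with 10, and 63–67% with all 14.

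**The case against.** The strongest reply is that no error has been shown. Bonferroni controls the error it is meant to control, is prespecified, and needs no assumption about dependence. On this view, asking for Holm is a reviewer's preference, and the detail could sit in an analysis plan that is not shown. The first part stands: the choice is valid and no passage conflicts with it. The second part carries less weight, because the article itself names the method and Holm is better or equal in every case at the same error rate.

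A second reply is that Bonferroni allows simple matching simultaneous intervals and Holm does not. That is a real trade-off. A reader might infer that the plan gives up power for nothing in return; as a general statement that goes too far. What can be said is that this plan reports ordinary 95% intervals and describes no adjusted ones, so it does not use the advantage.

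A third reply is that the size is uncertain and mostly small. This stands. The article supports neither the assumed 80% power for every outcome nor any particular m. A reader who looks at the largest gains might also conclude that the bone findings are seriously weakened by the choice of Bonferroni over Holm. Those gains require every outcome in the family to be truly affected and equally well powered, and the article gives no basis for expecting that.

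Two neighbouring matters are separate and are not cured by Holm: the family differs between the outcome list and Table 2, and the secondary sample sizes use an unadjusted 0.05. Holm-adjusted p values need a defined m just as Bonferroni does.

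**Conclusion.** The point holds as an optional, low-cost improvement, not as an error in the plan. Holm's superiority in rejections at equal familywise error is a mathematical fact and depends neither on m nor on the correlation.

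The size of the gain does depend on assumptions. With 80% power per true effect and m between 9 and 25, it is nil for the first rejection and about 1 to 4 points of average power when several effects, up to about half of the family, are real. It is about 7 to 12 points only if all are. The documents do not support a claim that the secondary analyses are invalid, or that a large loss is likely.

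**What to change.** In the remarks under Table 2, replace the words naming the Bonferroni method with the Holm step-down procedure at familywise two-sided 0.05. Report Holm-adjusted p values for the secondary outcomes, and label the 95% confidence intervals as unadjusted for multiplicity.

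The cost is one phrase in the table and one reporting note. The sample size and data collection do not change. The article describes recruitment as still active and the statisticians as blinded to allocation, so at that stage the change could be made without knowledge of results. The one thing given up is the option of simple simultaneous intervals that match the tests. If the sponsor wants such intervals, keeping Bonferroni and stating that the intervals are adjusted would be a coherent alternative.

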## Methods/design

### Trial design

The BHIP study is a two-arm, two-site prospective RCT. This study is designed as a prospective superiority trial, with 1:1 allocation ratio to either the Intervention group (i.e. Nutrition + Exercise intervention: high-dairy nutrition intervention combined with structured exercise) or the Control group (i.e. usual care as per National Health Canada recommendations) during pregnancy. The study is open-label with blinded endpoints. The study protocol is described following the standard protocol items: recommendations for interventional trials (SPIRIT) guidelines [34]. See Additional file 1 for the SPIRIT checklist and Additional file 2 for the WHO trial registration data set.

The core BHIP trial follows women up to delivery as the primary outcome relates to GWG. The Bone-BHIP study is an extension of the core BHIP trial that continues a follow-up of the women and their offspring until six months after delivery, with the objective to assess maternal and infant bone status. This trial is registered at ClinicalTrial.gov (NCT01689961). The BHIP trial is conducted by collaborative research teams at McMaster University (Hamilton, ON) and Western University (London, ON) in Canada. The study takes place in academic hospitals and community healthcare clinics in London, Burlington, and Hamilton, Ontario, Canada. Recruitment is facilitated by healthcare professionals (e.g. family doctors and midwives) who ask their patients for consent to be contacted by the BHIP study team, as well as poster advertisements in midwifery, family practice, and ultrasound clinics, at community sites such as the YMCA, libraries, and coffee shops, and on Facebook or Kijiji.

Study recruitment began in January 2013 and is expected to be completed by April 2018, reaching the a priori calculated sample size of 242 participants for our primary outcome. All participants who sign consent to contact forms receive a phone call by study personnel and are provided a general overview of the study and expectations using a scripted text. Figure 1 outlines the participant’s timeline in the BHIP study. Participants are screened for eligibility during the telephone interview according to the criteria list below. Eligible women are enrolled in the study and sign informed consent by the end of the first trimester of pregnancy (i.e. 12–17 weeks of gestation).

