### Randomization: allocation and implementation

Block randomization is used with block sizes of two, four, and six selected at random, using an online Research Electronic Data Capture (REDCap) randomization service managed by an independent team in the Biostatistics Unit at St Joseph’s Healthcare in Hamilton, ON, Canada. Randomization to the two study arms occurs in a 1:1 ratio and is stratified by study site and pre-pregnancy BMI category following IOM guidelines (underweight: BMI < 18.5, normal weight: BMI 18.5–24.9, overweight: BMI 25.0–29.9, and obese: BMI ≥ 30.0 kg/m^2^). The eligibility of participants is confirmed at the first visit, when baseline data are also collected. The research assistant randomizes the participant at the second visit to the study center using an online third-party automatic randomization system. Once randomized, the research assistant consents the participant to the appropriate study arm at a time that is 14–17 weeks/6 days of gestation. Assessments, regardless of the study arm, occur at < 18 weeks of gestation, 26–28 weeks of gestation, 36–38 weeks of gestation, birth, three months postpartum, and six months postpartum. The intervention arm consists of weekly or biweekly in-person visits (based on the participant’s preferences) during pregnancy (i.e. from allocation to study group until 36–38 weeks of gestation). Baseline measures (i.e. before randomization), primary and secondary outcome measures, and other measures assessed during and after pregnancy are measured in all participants, regardless of their study group allocation.

The flow diagram (Fig. 2) will be included in future published results.

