For the timely recruitment of study participants, challenges included prolonged ethics approval processes at secondary recruitment sites, reduced recruitment at community family practices due to influx of immigrants who were non-English speaking (thus not eligible), and competition with other studies sampling pregnant women. In light of these, we have taken measures to achieve the predetermined sample size based on a power analysis for the primary outcome so that the integrity of the study is preserved and the results are able to properly test the stated hypothesis and provide the needed new knowledge. To expand recruitment at McMaster University a new local study site was set up in a nearby city, Burlington, Ontario, with the collaboration of midwifery and obstetric clinics, as well as the local hospital. This partnership is very successful thus helping to achieve the recruitment goal. To date, retention after randomization to the study visit at 36–38 week of gestation when we assessed our primary outcome is 87%. To maximize retention of participants, we implemented a number of procedures such as study visit times at the convenience of the participants, including home visits. We also offered in-person, over the phone, and email correspondence to keep participants engaged. For participants in the intervention group, providing them with the dairy products (which are an integral part of the intervention) increases the likelihood of consuming the recommended amount. For the exercise component, participants receive a free pedometer as a self-motivation tool to reach their step count goals. Lastly, for both groups, participants are compensated on three occasions with $25 gift cards that they can redeem at a local grocery store.

If effective, this RCT will generate high-quality evidence to refine the nutrition guidelines during pregnancy to improve health of women during pregnancy and their offspring in early life, including acquisition of a strong skeleton.

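### GEE and random-effects checks on the primary outcome take site as the cluster, but there are only two sites: the usual GEE robust test would be badly anti-conservative and the random site effect adds almost nothing

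*Protocol article*

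**What the plan says.** - **Number of sites.** Trial design: "The BHIP study is a two-arm, two-site prospective RCT". The Discussion adds that, to expand recruitment at McMaster University, "a new local study site was set up in a nearby city, Burlington, Ontario". Power calculation lists "site (2 degrees of freedom"; two sites use one degree of freedom, so that entry would fit three levels.
- **Randomization.** Women are allocated individually, 1:1, "stratified by study site and pre-pregnancy BMI category following IOM guidelines" (Randomization section). Each site therefore contains both arms.
- **Main analysis.** Logistic regression for the primary outcome (Table 2, row 1). Under Statistical methods: "All analyses will account for stratification by including study site and participants’ BMI category in the models".
- **Sensitivity analyses.** Table 2, row 4 lists GEE and a random-effects model, with scope "Primary outcome only". The remarks under the table say that GEE "allows to specify the correlation structure between patients within a site", and Statistical methods refers to "the random-effect model which account for the potential correlation within sites". The cluster is thus the site.
- **Missing data.** The same remarks give GEE a second role: it is to cope with data missing at random, with a weighted form otherwise. Statistical methods separately plans multiple imputation.
- **Not stated.** Whether GEE uses sandwich or model-based standard errors, and any small-sample correction.

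**The concern.** The sandwich variance in GEE is justified when there are many independent clusters. With two, it is built from two site contributions that must cancel, so the standard error of the treatment effect reflects a single chance contrast between sites. A random site effect has a related weakness, since a variance has to be estimated from two values.

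There is also little for either model to correct. Treatment varies within site and site is already a covariate in every model.

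Statistical methods gives these analyses the purpose of assessing robustness, and Table 2 asks for an estimate, a 95% interval and a p value in all analyses. A site-clustered GEE could put a very small p value and a narrow interval beside a non-significant primary result, or give false reassurance beside a significant one.

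**Working it through.** The plan gives no operating figure for these analyses beyond the two-sided 5% level, so that level is the benchmark.

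**Inputs from the protocol article.** Two sites; 242 women; individual 1:1 allocation stratified by site and BMI; binary outcome; two-sided 0.05; site as the cluster.

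**Assumptions, not in the article.** Site shares 60/40 and 80/20 (45/35/20 for three sites); success rate 35% or 45%; between-site SD 0, 0.3 or 0.6 on the logit scale; BMI mix 50/30/20%.

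**Step 1: algebra for two sites.** Let site k hold a share w_k of the women and have within-site log odds ratio d_k. Take the pooled estimate as b = w1·d1 + w2·d2 (large samples, similar event rates).

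- Site 1 contributes w1(d1 − b) = w1·w2·(d1 − d2) to the sandwich. Site 2 contributes the exact negative.
- Sandwich variance = 2·w1²·w2²·(d1 − d2)².
- If V is the true variance of b, then var(d_k) = V/w_k and var(d1 − d2) = V/(w1·w2). Also, d1 − d2 is uncorrelated with b.
- Hence under no effect b/SE = (Z1/|Z2|)/c, with c = √(2·w1·w2) and Z1, Z2 independent standard normals. This is a scaled Cauchy variable, not a normal one.
- P(|b/SE| > 1.96) = 1 − (2/π)·arctan(1.96·c).

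| Split | c | 1.96·c | arctan | Null rejection |
|---|---|---|---|---|
| 50/50 | 0.707 | 1.386 | 0.946 | 39.8% |
| 60/40 | 0.693 | 1.358 | 0.936 | 40.4% |
| 80/20 | 0.566 | 1.109 | 0.837 | 46.7% |

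Equal sites are the most favourable case, so in this approximation no split does better than about 40%. The median of |Z2| is 0.674, so the median sandwich SE is 0.674·c of the true SE: 0.47 at 60/40 and 0.38 at 80/20.

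**Step 2: simulated type I error at nominal 5%** (242 women; 3,000 runs per main GEE setting, 500 per random-intercept setting).

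| Analysis | Type I error |
|---|---|
| Logistic, site fixed (the planned main model) | 4.9% to 5.4% |
| GEE, site-clustered sandwich, two sites, 60/40 | about 41% |
| Same, 80/20 | about 48% |
| Same, 60/40, site SD 0 to 0.6 | 39% to 41% |
| Same, with site added as a covariate | 40% to 48% |
| Same, three sites | about 28% |
| Sandwich with t reference on (sites − 1) df | 7% to 8% |
| GEE, model-based SE | 4.8% to 5.1% |
| Random site intercept, two sites, site SD 0 / 0.3 / 0.6 | 4.8% / 5.6% / 4.6% |
| Check: sandwich with 40 clusters | 4.8% |

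The median ratio of sandwich to model-based SE was 0.47 (60/40) and 0.39 (80/20), close to Step 1. The 40-cluster check shows that the cause is the number of clusters. Separate simulations with other seeds and settings extend the ranges to about 37% to 48% for two sites and 25% to 28% for three.

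**Step 3: the random intercept.** Its treatment test holds its level; with 500 runs the Monte Carlo SE is √(0.05·0.95/500) = 1.0 percentage point. The estimated site variance, however, fell to about zero in 83%, 58% and 40% of runs at true site SD 0, 0.3 and 0.6. Where it does, the model reduces to one with no site term, so it says little that the fixed-site model does not.

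**The case against.** **The standard error is not specified.** This is the strongest point, and it stands. Nothing in the article commits GEE to a sandwich estimator. With model-based errors the test keeps about 5%, and with a t reference on (sites − 1) df it is 7% to 8%. Such detail could sit in a statistical analysis plan that is not shown. The inflation must therefore be stated as conditional. The point survives because the article does fix the method, the cluster and the number of clusters, and the usual robust form of that combination fails. With model-based errors and site already in the model, GEE adds little to the main analysis.

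**The list of methods is illustrative.** Statistical methods introduces it with an e.g., but Table 2 names both models without qualification.

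**There may be three sites.** Trial design says two, while the Burlington site and the two degrees of freedom leave room for three. That lowers the rate to about 25% to 28%, which is still no usable check.

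**Stronger readings that the documents do not support.** A reader might infer that the random-effects model also produces false significance. It does not: allocation is within site, and its type I error was 4.6% to 5.6%. A reader might also infer that these analyses could overturn the primary conclusion. The article gives them no decision role, and the primary test is the logistic model with site and BMI category, which holds its level.

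**GEE also has a missing-data role.** This is correct, so removing it without a replacement would leave a gap.

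**Conclusion.** The concern holds in a limited form. If GEE is run with site-clustered sandwich errors and a normal reference, its false-positive rate is about 37% to 48% with two sites and about 25% to 28% with three, against a nominal 5%. The condition is an assumption about software practice, not something the article states. The site shares, event rates and between-site variation are also assumed, but the result is stable across them and the algebra puts the two-site rate at about 40% or more for any split.

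The random site intercept is valid for the treatment test but close to redundant. The primary analysis is unaffected. What is at stake is how the robustness results are read, so this is worth correcting but does not threaten the trial's main inference.

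**What to change.** Amend Table 2, row 4, its remarks and the matching sentence in Statistical methods:

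1. State that site-clustered sandwich inference will not be used.
2. Keep site as a fixed effect, with individual-level standard errors (model-based or heteroskedasticity-robust) or a permutation test stratified by site and BMI category.
3. Drop the random site intercept, or describe it as redundant with the fixed-site model.
4. Meet the missing-data role given to GEE through the multiple imputation already planned, with a sensitivity analysis for data not missing at random.
5. Say whether Burlington counts as a separate site, and align the degrees of freedom in Power calculation with that count.

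Site-specific estimates are an optional addition. The cost is plan wording only, settled before unblinded analysis; design, data collection and participant burden do not change.
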